# 7.3. Recording of adverse events and follow-up

If any adverse events occurred, especially those associated with the study drug, should be followed up until the patients return to baseline or tend to stabilize. If the baseline status or stability cannot be restored after follow-up, it should be noted in the CRF. All SAEs have to be reported within 24 hours, whether or not considered causally related to the investigational product, or to the study procedure(s).

# 7.4. Adverse events based on examinations and tests

The results from protocol mandated laboratory tests and vital signs will be summarized and give possible interpretation. The abnormal laboratory results caused by reported adverse events should be recorded in the adverse event form. The abnormal results with clinical significance that meets one or more following conditions should be recorded as independent diagnosis on adverse event page of CRF (excluding abnormal laboratory result caused by reported adverse events):

- With associated clinical signs and symptoms
- Change in course of study drug’s treatment dose
- Change in any of standard evidence based medications and (or) other treatment measures need to be changed

# 8. Blinding and Unblinding

**8.1 Methods for ensuring blinding**

The blinding of treatment is ensured by using a double-blind technique. The Qiliqiangxin capsules and the respective placebo capsules will be identical in size, colour, smell, and taste. The bottles with IP will be labelled with unique identification numbers.

# 8.1.1 Random grouping of subjects

Statistical experts at Peking University Clinical Research Institute adopts SAS 9.4 statistical software package to generate random numbers using the block randomization method according to the ratio of 1:1 between study group and control group. The study drug (Qiliqiangxin or placebo capsules) was packaged according to this random number by the person unrelated to the study.

A randomization and trail supply management system (RTSM) is used in the study, and statistical professionals will provide a random numbered list to the RTSM. The patient is then assigned a random number by the RTSM.

After completing baseline assessment, random numbers are assigned by RTSM during baseline visits. After that, the drug number is obtained through the RTSM according to the interview plan, and the serial number of drug assigned each time is different, but the drugs are the same. Before randomization of patient, the researcher must first log into the RTSM and provide the according information (e.g. the subject's date of birth, gender).

# 8.2. Methods for unblinding

[figure not shown]
Individual treatment codes, indicating the randomised treatment for each patient, will be available to the investigator(s) or pharmacists from the RTSM in case of adverse events. When the appropriate management of the patient requires knowledge of the treatment randomization, emergency unblinding can be proceeded. Researchers need to login RTSM and fill out the unblinding application, which would be reviewed by the main investigator. If unblinding is deemed necessary, the investigator can perform the unblinding in RTSM and must document all actions taken. Then, unblinding could be proceeded by the unblinding applicant. Clinical data for the above mentioned events will be evaluated and recorded as withdrawal case or AEs/SAEs.

# 8.2.1. Unblinding provisions

All personnel involved with the analysis of the study will remain blinded until database lock and protocol violations have been identified and documented The study adopts two-step unblinding provision. After blind check, the data is locked, main researchers, medical statisticians, data administrators and sponsor representatives will do the first unblinding, and the random number corresponding to the group will be marked as A or B, in order to make statistical analysis on all data. At the end of statistical analysis when summary report is completed, a secondary unblinding would be taken to reveal the group of A and B.

# 8.3. Screening number

The screening number was made according to the sequence of patients taking treatment at each hospital, and represented with center ID + three integers, such as the screening number is 01001, 01002 ….. for center 01.

# 9. Statistical Analysis

After determining study program, statistical professionals should take responsibility of formulating statistical analysis plan after consulting with main researchers. Sample size is estimated by PASS13. SAS®9.4 software (or higher version) is adopted for statistical analysis.

# 9.1. Definitions of analysis sets

- Full Analysis Set (FAS): refers to the data set obtained by removing the subject with the least intentional and reasonable methods from all randomized subjects as close as possible to the intention to treat. It contains all subjects who have been randomized and used study drug once. Exclusions usually included violations of important inclusion criteria, subjects not receiving treatment with the study drug, no observations after randomization. The main efficacy evaluation index was the time when the composite endpoint event occurred, and the survival analysis method was adopted for analysis. When the FAS was selected for statistical analysis, the loss of the primary endpoint event was treated according to the censorship.
- Per Protocol Set (PPS): A subset of the full analysis set, and these subjects are more compliant with the program. Subjects included in the PPS generally have the following characteristics: (1) Take the minimum exposure of study drug set in advance, that is, the compliance of taking the drug is 80%; (2) Main indicators are available in the study; (3) There was no major violation of the study protocol.
- Safety Set (SAS): All subjects who received at least one treatment after randomization and had a safety assessment. Security missing values do not need to be carried over.

# 9.2. Statistics methods

Efficacy analysis is taken on the basis of FAS and PPS. All baseline demographic data analysis will be performed on the basis of FAS and safety evaluation on SAS.

- All data are performed with two-sided test, and P value less than or equal to 0.05 (two-sided test) is considered with statistical difference (unless otherwise specified).
- Descriptive analysis: Classification data is described with number of cases and percentage. Quantitative data is described with mean, standard deviation, maximum value and minimum value, median, the first quartile (Q1) and third quartile (Q3).
- Comparison of general situation should be analyzed with appropriate method based on the type of index. Quantitative data should be analyzed with paired t test or Wilcoxon rank sum test; classification data with chi-square test or precise probability method, and grade data with Wilcoxon rank-sum test or CMH test.

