| **Outcome Measures** | Primary endpoints | The composite endpoint events consisting of cardiovascular death and re-hospitalization due to the worsening of heart failure |
| Secondary endpoints | 1. All-cause mortality 2. Secondary endpoint events (given up treatment due to worsening heart failure, successful resuscitation after cardiac arrest, malignant arrhythmia, non-fatal stroke) 3. The incidence of cardiovascular death and re-hospitalization due to worsening heart failure in patients with ischemic heart disease 4. Serum NT-proBNP decrease rate |
| Safety objective and measure | To evaluate the safety and tolerability of QLQX in this patient population;  Changes in clinical chemistry/haematology parameters, ECG, physical examination, any forms of adverse events (AEs) |
| **Statistical methods** | The primary objective of the study is to determine the superiority of QLQX versus placebo in reducing the incidence of the primary composite endpoint. The random distribution ratio is 1:1 between study group and control group. The sample size is in estimating the incidence of composite endpoint events for 25% during the follow-up period of 36 months. In total 3080 cases were expected to enroll (1540 patients per group) with 620 composite endpoint events should be observed. | |
| **Statistical unit** | Peking University Clinical Research Institute | |
| **Dosage and mode of administration** | Study group: Standardized treatment of chronic heart failure + Qiliqiangxin Capsules, 4 capsules/time, 3 times/day, take orally  Control group: Standardized treatment of chronic heart failure + Placebo Capsules, 4 capsules/time, 3 times/day, take orally | |
| **Duration of treatment** | The patient was enrolled with observation event as the index. The planned enrollment time was 2 years and the drug was taken for at least a year. | |
| **Expected progress** | August 2018 to August 2021 | |

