# 2. Study design

# 2.1. Rationale for study design

This study is a randomized, double-blind, placebo-controlled, parallel-group, multicenter clinical study.

The study will be event-driven, and all randomized patients will remain in the study (whether taking the study drug or not) until the number of primary endpoint events reaches the predicted value (620 cases), or the study terminates early when it meets the pre-defined efficacy or safety criteria of early termination.

Two mid-term efficacy analyses planned to be conducted after 1/2 and 2/3 primary endpoint events to assess whether an invalid or valid conclusion was reached so as to prematurely end the study.

The entire study will last approximately 36 months, and the recruitment period will be expected to be 24 months. The follow-up period after the last case of patient is included in the study is 12 months. The average follow-up time is predicted to be about 24 months.

Patients who show stable clinical symptoms, had received at least 2 weeks of standardized treatment and treatment of other concomitant diseases before enrollment are screened at the hospital. According to the local HF treatment guidelines, the drug type and dosage are fixed, unless it is contraindicated or intolerant. The patient who have not receive anti-HF drug intravenously for at least two weeks prior to enrollment, nor take oral administration of TCM or Chinese patent medicine having similar composition with Qiliqiangxin Capsule can directly enter the random grouping stage.

If patients fail to meet the above requirements, term standardized treatment to meet the above criteria before entering the random grouping stage are needed.

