# 2.2. Control group and Sample size

According to the PARADIGM-HF study, cardiovascular death or hospitalization rate for heart failure in the median follow-up of 27 months was 21.8% in the LCZ696 group and 26.5% in the Enalapril group. Therefore, we estimate that the incidence of cardiovascular death and hospitalization for heart failure is 25% in all patients of basic treatment +placebo group within 36 months of follow-up and 20% in basic treatment + Qiliqiangxin Capsule group.

The random distribution ratio is 1:1 between study group and control group. Considering the consumption of type I error in the interim analysis, α is adjusted to unilateral 0.02314. The sample size is the number of cases with composite endpoint events. It is expected that 620 composite endpoint events need be observed to provide 80% power of test (β= 0.2), and 20% risk can be reduced in study group by log-rank test.

The entire study will last approximately 36 months to follow up, and the recruitment period are expected to be 24 months. It is expected that 3,080 patients in over 100 centers (1540 patients per group, 1:1 into study group and control group) will be enrolled and be followed up at least for 12 months. Estimating the incidence of composite endpoint events is 25%, in total 620 end-point events are expected to be obtained in the analysis.

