# 4.1.2 . Secondary outcome measures

- All-cause mortality
- Secondary endpoint events (given up treatment due to worsening heart failure, successful resuscitation after cardiac arrest, malignant arrhythmia, non-fatal stroke)
- Cardiovascular death and re-hospitalization due to worsening heart failure in patients with ischemic heart disease
- Level of Serum NT-proBNP

*Note: All endpoint events should be determined and reviewed by Clinical Event Adjudication Committee.*

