# 9.2.3 . Efficacy analysis:

- PP analysis and FAS analysis were performed simultaneously with efficacy evaluation;
- Main efficacy evaluation index is the time when a composite endpoint event (cardiovascular death and re-hospitalization for deterioration of heart failure) occurs. The lack of primary endpoint events is considered as censored data.

The main research hypotheses are:

H0: λT / λC ≥ 1

H1: λT / λC < 1

λT and λC are the risk of endpoint events in the study group and control group respectively. The Kaplan-Meier method was used to estimate the incidence of clinical endpoints, and a Log rank test was performed for analysis between the two groups. COX proportional hazard model was used and the center was served as a covariate to estimate the hazard ratio and the 95% confidence interval. The composite endpoints, cardiovascular death and rehospitalization for deterioration of heart failure, were analyzed separately.

- - Secondary efficacy indicators:
    - All-cause mortality
    - Composite endpoints (given up treatment due to worsening heart failure, successful cardiac arrest after resuscitation, malignant arrhythmia, non-fatal stroke)
    - Cardiovascular death and re-hospitalization for decompensated heart failure in patients with coronary heart disease
    - Serum NT-proBNP: statistical analysis of measurement data between groups.

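### Section 9.2 names a paired t test although the arms are independent, and the NT-proBNP secondary endpoint is a decrease rate in the synopsis but a level in Section 4.1.2

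*Protocol*

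**What the plan says.** **Test for quantitative data.** Section 9.2 introduces its list of tests with "Comparison of general situation should be analyzed with appropriate method based on the type of index", and continues: "Quantitative data should be analyzed with paired t test or Wilcoxon rank sum test". No other part of the protocol names a test for quantitative data. Section 9.2.1 then lists demographic characteristics, medical history and medication history for comparison between the groups.

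**Design.** Section 2.1: "This study is a randomized, double-blind, placebo-controlled, parallel-group, multicenter clinical study". Section 2.2: "The random distribution ratio is 1:1 between study group and control group", with 3,080 patients planned ("1540 patients per group, 1:1 into study group and control group").

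**NT-proBNP as a secondary endpoint.**
- Synopsis: "Serum NT-proBNP decrease rate"
- Section 4.1.2: "Level of Serum NT-proBNP"
- Section 9.2.3: "Serum NT-proBNP: statistical analysis of measurement data between groups"

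Section 9 foresees a separate statistical analysis plan, which was not available.

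**The concern.** A paired t test needs natural pairs, usually two measurements on the same patient. A patient on the capsule has no partner on placebo. Used here, the test either matches patients across arms arbitrarily or measures change over time within one arm, which is not a treatment comparison. The sentence is also at odds with itself. The rank-sum test is for independent groups, and the non-parametric partner of a paired t test would be the signed-rank test. The likeliest explanation is a slip for the two-sample (group) t test.

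The NT-proBNP difficulty is separate. A decrease rate needs a baseline and a follow-up value, while a level needs only the latter. An SAP cannot follow both the synopsis and Section 4.1.2, so whichever it adopts departs from one of them, and the choice could be made late. The endpoint has some weight, because Section 1.3 presents NT-proBNP reduction as the ground on which this trial was built.

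**Working it through.** The protocol states no sample size, power or effect for NT-proBNP, so there is no figure of its own to reproduce. The steps below set the passages side by side and size the consequence.

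**1. Named test against design.** Inputs from the protocol: independent arms, 1,540 per arm, two-sided 0.05. Assumed: log-scale SD 1.0, baseline-to-follow-up correlation r = 0.6, an identical mean fall of 0.2 in both arms (no treatment effect). In 4,000 simulated trials, the share with P ≤ 0.05 on the change score was:

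| Test | Rejections |
| --- | --- |
| Rank-sum between arms | 4.75% |
| Two-sample t between arms | 4.5% |
| Paired t, patients matched arbitrarily across arms | 4.5% |
| Paired t within one arm | 100% |

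The last row follows directly. The SD of change is √(2(1 − 0.6)) = 0.894, its standard error 0.894/√1540 = 0.0228, and 0.2/0.0228 = 8.8 standard errors. The test detects the fall over time and says nothing about treatment. Arbitrary matching holds its error rate, but the result depends on an ordering with no meaning, and it cannot be run when the arms differ in size.

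**2. The NT-proBNP wordings.**

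| Place | Variable | Settled? |
| --- | --- | --- |
| Synopsis | Decrease rate | Could be a relative change, or the share of patients with a decrease |
| Section 4.1.2 | Level | A value, not a change |
| Section 9.2.3 | Measurement data | Gives a data type, no variable and no test |

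Section 1.3 reports both kinds of result from the earlier capsule study: an NT-proBNP ratio, and the share of patients with a decrease above 30%. The second is categorical and would fall under the chi-square or exact test in Section 9.2. The Section 9.2.3 wording leans away from that reading but does not decide between a level and a continuous change.

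For a continuous variable with equal SD at both times, variance of change ÷ variance of level = 2(1 − r):

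- r = 0.3: 1.4
- r = 0.5: 1.0
- r = 0.6: 0.8
- r = 0.7: 0.6
- r = 0.8: 0.4

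On the log scale, randomisation gives a level and a change the same expected between-arm difference, so the choice affects precision and sensitivity to chance baseline imbalance. A percentage decrease or a responder share is a different quantity altogether.

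**3. Optional baseline adjustment (correlations assumed).** Variance of a baseline-adjusted comparison (ANCOVA) relative to level = 1 − r²; relative to change = (1 + r)/2. Power is for an assumed log difference of 0.10, SD 1.0, 1,540 per arm, two-sided 0.05.

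| r | ANCOVA ÷ level | ANCOVA ÷ change | Power: level | Power: change | Power: ANCOVA |
| --- | --- | --- | --- | --- | --- |
| 0.5 | 0.75 | 0.75 | 79% | 79% | 89% |
| 0.6 | 0.64 | 0.80 | 79% | 87% | 93% |
| 0.7 | 0.51 | 0.85 | 79% | 95% | 97% |

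For r from 0.5 to 0.7, variance therefore falls by 25% to 49% against levels and by 15% to 25% against change.

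**The case against.** The strongest reply concerns scope. The quoted sentence belongs to a bullet on the general situation, which reads most naturally as general or baseline characteristics. NT-proBNP is handled in Section 9.2.3, which names no test and does not refer back. A reader might infer that NT-proBNP will be analysed by a paired t test; the protocol does not say so. This stands, and it narrows the point. It does not rescue the sentence, because baseline characteristics are also compared between groups.

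Three further objections hold:
- **Validity.** The same sentence offers the rank-sum test, which is valid for independent arms and unaffected by a log transformation of levels. The plan for quantitative data as a whole cannot be called invalid.
- **Regression to the mean.** A reader might fear that within-arm falls after selection on NT-proBNP of at least 450 pg/ml would be read as efficacy. Section 9.2.3 plans a between-group analysis, so that harm is hypothetical. The before/after comparisons in Section 9.2.4 are safety items, and a paired test would be proper for the vital signs there.
- **Silence is not error.** Log scale, baseline covariate and model may be left to the SAP. An unadjusted randomised comparison is less efficient but not wrong. Nor can a missing visit be charged, since the schedule in Section 5 is a figure that was not available.

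It would also overstate matters to count three definitions of NT-proBNP: two conflict, and the third wording is merely unspecific.

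**Conclusion.** Two errors in the protocol's own text stand. The paired t test is the wrong parametric test for comparing independent arms, whichever quantitative variables Section 9.2 is meant to cover. The synopsis and Section 4.1.2 name different NT-proBNP variables, and Section 9.2.3 does not settle which applies. Neither depends on an assumed figure. The assumptions (correlation, SD, size of the fall and of the treatment difference) serve only to size the consequence.

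The impact is modest: general or baseline comparisons and one of four secondary endpoints. The primary log-rank and Cox analysis, the event endpoints and the sample size are untouched. Baseline adjustment is advice, not a finding.

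**What to change.** 1. In Section 9.2, replace the paired t test with the two-sample (independent-groups) t test for between-arm comparisons, keeping the rank-sum alternative. Reserve paired tests for before/after summaries within patients.
2. Choose one NT-proBNP variable and state it in the same words in the synopsis, Section 4.1.2 and Section 9.2.3. If the decrease rate is kept, say whether it is a relative change or the share of patients reaching a stated decrease.
3. Optionally, in the SAP, analyse log NT-proBNP with baseline log NT-proBNP as covariate and report the ratio of geometric means with its 95% confidence interval.

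Items 1 and 2 cost a few words in a protocol amendment and no new data. Item 3 uses baseline values that the NT-proBNP entry criterion already requires. All three should be settled before unblinding.

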# 9.2.1. Enrollment and completion

The following information would be initially analyzed:

- Summarize the number of enrollment and completion of each center;
- Detailed list for the number of falling off and withdrawal cases, and the total abscission rate;
- Group size in different data sets;
- Case distribution of each center
- Demographic characteristics (age, height, weight, vital signs, etc.), medical history and medication history between groups

# 9.2.2 Compliance analysis:

- Medication compliance analysis: comparison between two groups of the investigational drug intake condition (e.g. timely and correct intakes, prohibited medicine and food of the scheme, etc.)
- Drug combination analysis: analysis for the detailed list of drug combination in each group;

# 9.2.3 . Efficacy analysis:

- PP analysis and FAS analysis were performed simultaneously with efficacy evaluation;
- Main efficacy evaluation index is the time when a composite endpoint event (cardiovascular death and re-hospitalization for deterioration of heart failure) occurs. The lack of primary endpoint events is considered as censored data.

The main research hypotheses are:

H0: λT / λC ≥ 1

H1: λT / λC < 1

λT and λC are the risk of endpoint events in the study group and control group respectively. The Kaplan-Meier method was used to estimate the incidence of clinical endpoints, and a Log rank test was performed for analysis between the two groups. COX proportional hazard model was used and the center was served as a covariate to estimate the hazard ratio and the 95% confidence interval. The composite endpoints, cardiovascular death and rehospitalization for deterioration of heart failure, were analyzed separately.

- - Secondary efficacy indicators:
    - All-cause mortality
    - Composite endpoints (given up treatment due to worsening heart failure, successful cardiac arrest after resuscitation, malignant arrhythmia, non-fatal stroke)
    - Cardiovascular death and re-hospitalization for decompensated heart failure in patients with coronary heart disease
    - Serum NT-proBNP: statistical analysis of measurement data between groups.

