Due to the economic improvement, diet change, and also the extending of human life, the incidence of heart failure increases with age [8]. Also, with the development of modern medicine, the mortality rate of patients with heart failure has gradually decreased, but remains in a relatively high level. The 1-year mortality rate of patients with heart failure over 70 years old is significantly higher than that of patients under 70 years old (22%: 13.7%) in the United States [9]. The 1-year and 3-year mortality rates of heart failure patients are 11.3% and 29.2% in Japan, respectively [10]. In Europe, the 4-year survival rate is only 50%, and 40% of heart failure inpatients is admitted to hospital for treatment or dies within 1 year [11, 12]. Chronic heart failure is still a major problem that seriously threatens human life and quality of life which in need to be resolved.

In the past 20 years, the concept of drug treatment for heart failure has changed greatly, from the perspective of improving hemodynamics to the point of biological adjustment. The focus of modern treatment models is to improve the neuroendocrine disorders of the renin- angiotensin-aldosterone system and the sympathetic nervous system. Therefore, the goal of treatment is not only to improve symptoms and quality of life, but also to inhibit and delay the development of myocardial remodeling, terminate the vicious circle, thereby to reduce the mortality and hospitalization rate of heart failure.

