# 4. Outcome Measures for Analyses

# 4.1 Clinical observation endpoints

# 4.1.1 . Primary outcome measure

- - - The composite endpoint events consisting of cardiovascular death
    - Re-hospitalization due to the worsening of heart failure;

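### Kaplan-Meier is named to estimate endpoint incidence with death not treated as a competing event, which modestly overstates the incidence of heart failure re-hospitalisation alone (minor)

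*Protocol*

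**What the plan says.** Protocol section 9.2.3 (Efficacy analysis) names the estimator just after the primary hypotheses: "The Kaplan-Meier method was used to estimate the incidence of clinical endpoints". A log-rank test between the groups and a Cox model with centre as covariate follow, and then: "The composite endpoints, cardiovascular death and rehospitalization for deterioration of heart failure, were analyzed separately". The censoring rule given there is that a patient without a primary event is censored. No separate rule is given for death when the endpoint excludes death.

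Section 9.2.3 then lists the secondary indicators, among them "Composite endpoints (given up treatment due to worsening heart failure, successful cardiac arrest after resuscitation, malignant arrhythmia, non-fatal stroke". That composite contains no death, and no other incidence estimator is named for it. Section 4.1 places the primary and secondary outcomes together under the title "Clinical observation endpoints".

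Sections 6.1 and 6.2 send all deaths to central adjudication and have each death classified as cardiovascular or non-cardiovascular. The protocol mentions no cumulative incidence function or other competing-risk method.

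**The concern.** A patient who dies cannot later be re-hospitalised or have a non-fatal stroke. Kaplan-Meier for such an endpoint censors the patient at death, which treats the event as still possible. The resulting 1-KM describes a hypothetical population in which nobody dies first. It lies above the real incidence whenever deaths occur before the event. Cardiovascular death alone has the same problem on a smaller scale, because only non-cardiovascular death competes with it.

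What is at stake is the reported component incidence and any absolute risk difference or number needed to treat derived from it. If the drug changes mortality, the error differs between arms, so it does not cancel in the difference.

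**Working it through.** **Inputs.** From section 2.2: 25% composite incidence at 36 months on placebo and a planned 20% risk reduction. From section 2.1: mean follow-up of about 24 months. The protocol states no incidence for re-hospitalisation alone or for the non-fatal composite, so there is no planned component figure to reproduce. The following are assumptions:
- constant hazards;
- re-hospitalisation makes up 50 to 70% of the first-event hazard, and cardiovascular death the rest;
- non-cardiovascular death adds 0 to 50% to the cardiovascular death hazard.

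**Formulas.** With event hazard a, competing death hazard b and time t in years:
- 1-KM = 1 - exp(-a t)
- cumulative incidence = a/(a+b) × [1 - exp(-(a+b) t)]

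**Anchor.** The composite hazard is -ln(0.75)/3 = 0.0959 per year, which returns 25% at 36 months.

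**Worked case: 60% share, no non-cardiovascular death.** Here a = 0.0575 and b = 0.0384. 1-KM = 1 - exp(-0.0575 × 3) = 15.9%. Cumulative incidence = 0.6 × 25% = 15.0%. The gap is 0.85 points, or 6% relative. At 24 months the figures are 10.9% and 10.5%, a gap of 0.4 points.

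**Range at 36 months.**

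| Re-hospitalisation share | Added non-CV death | 1-KM | Cumulative incidence | Gap (points) | Relative |
|---|---|---|---|---|---|
| 50% | 0 | 13.4% | 12.5% | 0.9 | 7% |
| 50% | 50% | 13.4% | 12.1% | 1.3 | 11% |
| 60% | 0 | 15.9% | 15.0% | 0.85 | 6% |
| 60% | 50% | 15.9% | 14.6% | 1.3 | 9% |
| 70% | 0 | 18.2% | 17.5% | 0.7 | 4% |
| 70% | 50% | 18.2% | 17.15% | 1.1 | 6% |

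Over the same grid at 24 months the gap is 0.35 to 0.6 points (3 to 7% relative).

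**Simulation check.** With a 60% share, 20% added non-cardiovascular death and censoring spread over 12 to 36 months, the estimates at 2.9 years were 15.4% by 1-KM and 14.5% by Aalen-Johansen. The formulas give 15.4% and 14.4%.

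**Absolute difference at 36 months** (60% share, no non-cardiovascular death):
- Both hazards reduced by 20%. Kaplan-Meier: 15.85% - 12.90% = 2.96 points from unrounded values. Cumulative incidence: 15.00% - 12.33% = 2.67 points.
- Only the re-hospitalisation hazard reduced by 20%: 2.96 points by Kaplan-Meier and 2.80 by cumulative incidence.

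**Non-fatal composite.** If 1-KM is 5 to 20% at 36 months and 3-year mortality 10 to 20% (both assumed), the gap is 0.25 points (5% against 4.75%) to 2.0 points (20% against 18.0%), or 5 to 11% relative.

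**Primary composite.** Only non-cardiovascular death competes. An assumed 2 to 5% at 36 months moves 25.0% to between 24.8% and 24.4%.

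**The case against.** The case against making much of this has four parts.

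- **Scope.** The Kaplan-Meier sentence stands in the primary-hypothesis paragraph, and the secondary list that follows repeats no estimator. A reader might infer that the protocol fixes Kaplan-Meier for every clinical endpoint, but the text does not say so. Coverage of the two components follows from the adjoining sentence. Coverage of the non-fatal composite is inferred from the unrestricted wording and the title of section 4.1. This limit stands.
- **Place.** Competing-risk displays are often left to the SAP, which section 9 says will follow. That does not remove the point. The protocol names an estimator, and that estimator gives the wrong number for an endpoint that excludes death.
- **Size.** Section 1.3 says "The 1-year and 3-year mortality rates of heart failure patients are 11.3% and 29.2% in Japan", and a reader might take 29.2% as this trial's mortality, which would put the overstatement near 18% relative. The documents do not support that. By its title in the reference list, the source is a registry of hospitalised patients, whereas section 2.3.1 seeks patients with stable symptoms, mainly NYHA II to III. A monthly death hazard of 0.0096 (29.2% at 36 months) with a re-hospitalisation hazard of 0.0048 gives a composite of 1 - exp(-0.0144 × 36) = 40% if the deaths are cardiovascular, against the planned 25%. This objection stands.
- **Inference.** Log-rank and Cox compare cause-specific hazards and remain valid as such, so no confirmatory result changes. This also stands.

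**Conclusion.** The point holds and is minor. Applied as written, 1-KM overstates the incidence of heart failure re-hospitalisation alone. The direction is certain whenever deaths precede admission. The size rests on assumed component shares and constant hazards tied to the planned 25%: roughly 1 point at 36 months and half a point at 24 months. The absolute benefit in the worked case is overstated by 0.15 to 0.3 points.

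Two stronger conclusions should not be drawn. A reader might infer that the primary analysis is compromised. It is not: the test, hazard ratio, alpha, power and event count do not depend on this estimator, and the primary composite incidence moves by 0.2 to 0.6 points at most under the stated assumptions. A reader might also infer that risk differences are always inflated. That depends on the drug's effect on mortality, and the bias could reverse if mortality rose on treatment.

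**What to change.** In section 9.2.3, state that incidence is estimated by the cumulative incidence function (Aalen-Johansen), with:
- all-cause death as the competing event for heart failure re-hospitalisation alone and for the non-fatal secondary composite;
- non-cardiovascular death as the competing event for cardiovascular death alone.

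Keep Kaplan-Meier for all-cause mortality, which has no competing event. Keep log-rank and Cox, described as cause-specific analyses for these endpoints. A cumulative incidence estimate for the primary composite is optional because the change is negligible.

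The cost is a wording change. The adjudicated deaths and their cardiovascular or non-cardiovascular classification are already collected, and sample size and alpha are untouched. The downside is that reported component rates, and in the worked cases the absolute differences, become slightly lower.
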